## Methods

### Design

The study “Weed Care” is designed as a randomized, controlled, unblinded superiority trial with two parallel groups. Participants will be randomized to the experimental group with legal cannabis access in pharmacies or to the waiting list control group representing the illicit market. The primary endpoint is 6 months of regulated cannabis access. After 6 months, an observational study of 2 years will follow. During this time, both groups will have access to cannabis in pharmacies. This monocenter study will be conducted in the canton Basel-Stadt in Switzerland. The study has been approved by the local ethics committee “Ethikkommission Nordwest- und Zentralschweiz” (EKNZ) as well as by the Swiss Federal Office of Public Health. Furthermore, the study is designed in agreement with the Declaration of Helsinki, the ICH-GCP guidelines, and the Swiss law, notably the amendment of the Federal Act on Narcotics and Psychotropic Substances. The latter defines certain conditions for scientific studies with recreational cannabis such as minimum age of participants and maximum tetrahydrocannabinol (THC-) content (48).

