### Recruitment

A media conference in September 2022 informed the public about the current study. From this point on, interested persons were able to register online. After online registration, potential participants are contacted by phone for a first screening by the study nurse. Following, they are invited for a face-to-face interview with the study physician. In this interview, detailed information about the study is provided and written informed consent is obtained following the evaluation of inclusion/exclusion criteria. Individuals suitable for participation are randomly assigned to the experimental or control group. Furthermore, each participant will be asked to provide a blood sample. Recruitment has begun in September 2022 and will last until the required number of participants (*N* = 374) is reached, but no longer than 1 year.

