### Participant timeline

Figure 1 shows the participant flow through the study. Legal cannabis access in pharmacies started on January 30, 2023. Both groups—the experimental as well as the control group—were invited to answer the baseline-survey two weeks prior to cannabis access (see Table 1). Follow-up assessments, using the full battery, will be collected every 6 months from baseline (at 6, 12, 18, 24, and 30 months) with a total of five main follow-up assessments. Additionally, short follow-up assessments are conducted every 2 months (at 2, 4, 8, 10, 14, 16, 20, 22, 26, and 28 months) with a total of ten short follow-up assessments. Main assessments lasts approximately 30 min, short assessments 10 min. Participants are required to answer the main assessments within 2 weeks, in order to buy cannabis in pharmacies. If they do not answer the questionnaires, they will be blocked.

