Prevention: Pharmacists inform participants about lower-risk use guidelines such as products with lower THC content or vaporizers (62, 63). Furthermore, health prevention information and lower-risk use guidelines will be also available on the product packaging as well as on the study website.Early detection, early intervention, and encouraging treatment: Pharmacists may notice any potential health risks in participants. In this case, pharmacists will conduct a brief intervention and will recommend to contact the study physician, a local counseling or treatment institution. In case of a severe health risk, pharmacists may impose a consultation with the study physician. He will check whether legal cannabis access is still medically acceptable for this participant. The study physician trained all pharmacists on lower-risk cannabis guidelines as well as on red flags of cannabis use disorder, psychosis, depression, and suicidality. Besides the pharmacists, cannabis use disorder, depression, anxiety, and psychosis will be assessed every 6 months *via* online-assessments. If participants show a significant deterioration in one of these aspects, the study physician will contact the affected participant, will evaluate whether cannabis access remains medically responsible, and will provide treatment options.

The control group shall display the status quo in Switzerland, namely the situation of the illicit market. Therefore, during the first 6 months, the waiting list control group has no access to cannabis in pharmacies. They have to continue to obtain their cannabis *via* their usual sources. Additionally, any prevention information and early detection and intervention in pharmacies are lapsed for this group during the first 6 months.

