### Statistical methods

Descriptive statistics will be reported for sociodemographic and baseline characteristics. For the analysis of the primary outcome, analysis of covariance will be used (82). This model includes CUDIT-R mean after 6 months as dependent variable and the study group (experimental, control group) and the CUDIT-R mean at baseline as independent variable. Linear mixed models will be conducted for the analyses of the secondary outcomes in order to evaluate between-person and within-person differences during the 2 years of regulated cannabis access. Additionally, potential effect modification will be analyzed (gender, age, education, and cannabis consumption motives). Data will be analyzed according to the intention-to-treat-principle and thus (82), all patients being enrolled in the study and answered the baseline survey will be included.

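### The analysis set called intention-to-treat depends on answering a survey sent after randomisation in an open trial, so randomised people can be excluded at different rates by arm

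*Protocol article*

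**What the plan says.** All references are to the Protocol article.

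- **Statistical methods:** "Data will be analyzed according to the intention-to-treat-principle". The same sentence then restricts the set: "all patients being enrolled in the study and answered the baseline survey will be included". The primary model is an ANCOVA of 6-month CUDIT-R on study group and baseline CUDIT-R.
- **Recruitment:** after the interview, consent and eligibility check, "Individuals suitable for participation are randomly assigned to the experimental or control group". Recruitment began in September 2022.
- **Participant timeline:** both groups "were invited to answer the baseline-survey two weeks prior to cannabis access", and access opened on 30 January 2023. Also: "Participants are required to answer the main assessments within 2 weeks, in order to buy cannabis in pharmacies", and "If they do not answer the questionnaires, they will be blocked".
- **Design:** the study is "designed as a randomized, controlled, unblinded superiority trial with two parallel groups".
- **Interventions:** "during the first 6 months, the waiting list control group has no access to cannabis in pharmacies".
- **Limitations:** the authors expect that dropout may be high among controls, because some will not want to wait six months.

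**The concern.** Intention-to-treat keeps everyone who was randomised, in the arm to which they were allocated. Requiring a response to a survey that comes after allocation removes some randomised people because of something they did later. In an open trial, that behaviour can depend on the allocation itself.

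There is a plausible reason for it to do so here. When the survey arrives, the experimental group is about two weeks from legal access, while the control group faces a six-month wait. Controls who lose interest early are the people the Limitations section worries about. If they leave before the survey, they fall outside the analysis set altogether and do not count as dropouts within it.

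The primary comparison is then between two groups that randomisation alone no longer defines. A shift in either direction would matter. The Discussion reads a benefit as favouring regulation, a deterioration as favouring prohibition, and no difference as showing that the model is not inferior.

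**Working it through.** **1. Order of events.** Randomisation follows the eligibility interview, from September 2022. The survey invitation went out two weeks before 30 January 2023, to groups that already existed. For the earliest entrants the gap is up to about four months. The survey therefore follows randomisation, and the exclusion is a post-randomisation one.

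**2. The plan's own figure, for scale.** The Sample size section gives a 2-point difference, power 0.80, alpha 0.05, 20% dropout and 187 per group. Evaluable per group: 187 × 0.8 = 149.6. The article does not state the SD, so 187 cannot be reproduced independently, only solved backwards. With a two-sided test and 150 per group:

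SD = 2 / [(1.960 + 0.842) × √(2/150)] ≈ 6.18

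The standard error of the unadjusted arm difference is then 6.18 × √(2/150) ≈ 0.71. The SD is an assumption, and the point does not depend on it.

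**3. Size of a shift.** Let e be the share of an arm that skips the survey, and D the difference in 6-month CUDIT-R between skippers and those kept, beyond what baseline explains and equal in both arms. Leaving skippers out moves an arm mean by e × D, so

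shift in arm difference = (e_control − e_experimental) × D

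All rates and values of D below are assumed.

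| Skipping, experimental vs control | D = 2 | D = 3 | D = 6 |
|---|---|---|---|
| 2% vs 10% | 0.16 | 0.24 | 0.48 |
| 5% vs 15% | 0.20 | 0.30 | 0.60 |
| 2% vs 20% | 0.36 | 0.54 | 1.08 |
| equal in both arms | 0 | 0 | 0 |

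For the first row with D = 3: (0.10 − 0.02) × 3 = 0.24 points, which is 0.24/2 = 12% of the target. In people, this is about 187 × 0.02 ≈ 4 and 187 × 0.10 ≈ 19. The control mean alone moves by 0.10 × 3 = 0.30, but the experimental mean moves by 0.02 × 3 = 0.06 in the same direction, so the net figure is 0.24. If skippers have worse scores, the experimental arm looks worse than it should; if they have better scores, it looks better.

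**4. What the ANCOVA removes.** The 2% vs 10% pattern was simulated with no true effect and an assumed SD of about 6.18; case (a) used an assumed baseline-to-6-month correlation of 0.6.

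- *(a) Skipping depends only on baseline severity.* Excluded controls differed by 2.3 points at 6 months. The raw difference among those kept was biased by 0.19, close to 0.08 × 2.3 = 0.18. The ANCOVA in the protocol's set was biased by 0.00.
- *(b) Skipping depends on unmeasured factors related to the outcome.* The ANCOVA in the protocol's set was biased by about 0.3.

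**5. What filling in the covariate does.** In case (a), putting the overall mean in place of the missing baseline scores and analysing everyone randomised gave a bias of about −0.2, and a missing-indicator gave 0.00. In case (b) the indicator gives no protection. It fits skippers their own level, so the arm contrast still comes almost entirely from those who answered. Multiple imputation likewise rests on an assumption about why the score is missing.

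**6. Power.** If baseline non-response comes on top of the 20% dropout, the evaluable numbers at 2% vs 10% are 187 × 0.98 × 0.8 = 146.6 and 187 × 0.90 × 0.8 = 134.6. Power is then about 0.77 instead of 0.80, with SD 6.18.

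**The case against.** The strongest reply is that the article shows a mechanism and no more. Several stronger readings are tempting, and the text does not support them.

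- *That exclusion did differ by arm.* No response rate is given for either arm. Only the possibility follows from the text.
- *That the experimental group had to answer the baseline survey in order to buy.* The purchase rule names main assessments. The paragraph containing it uses that term elsewhere for the five follow-ups. The Data collection section divides all data into main and short assessments, and Table 1 gives baseline nearly the whole battery, so covering baseline is a natural reading, but it is not stated.
- *That controls had no reason to answer.* If the rule covers baseline, being blocked could also cost them two later years of access. The contrast is immediate against delayed reward.
- *That participants knew their arm when surveyed.* The article does not date disclosure. It is inferred from the open design and the existing groups.
- *That those excluded go unreported.* Nothing says so, and an article may leave participant flow to the full protocol.

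Two further points stand. The survey precedes access, so exposure to the product cannot cause the exclusion. The ANCOVA also removes whatever bias baseline severity explains.

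The practical defence, that the model needs a baseline score, does not save the definition. A missing covariate can be handled without dropping the person, and a control who skipped baseline may still answer at 6 months.

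**Conclusion.** The definition and its label contradict each other and need correcting. The set is modified intention-to-treat: it leaves out randomised people on the basis of a later response in an open trial, and it can do so unequally by arm. This rests on the article's own sequence of events and needs no assumed figure.

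The size is not known. Under the assumed 2% vs 10% skipping and a 3-point gap beyond baseline, the shift is about 0.24 points, or 12% of the target and about a third of the assumed standard error (0.24/0.71 = 0.34). It is about zero if skipping is equal with the same gap in both arms, or if it depends only on baseline severity. It reaches about 1.1 points only at the far end of the assumed range. The point supports a correction before analysis. It does not support a claim that the result is biased.

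**What to change.** 1. Define the primary set as all randomised participants, analysed as allocated, whether or not they answered the baseline survey.
2. Rename the present set modified intention-to-treat and keep it as a sensitivity analysis.
3. Report baseline-survey non-response by arm.
4. State how a missing baseline CUDIT-R is handled in the ANCOVA and on what assumption. Do not call it unbiased: overall-mean fill, a missing-indicator and multiple imputation can each be biased when missingness depends on arm.
5. Add an analysis of all randomised participants with a 6-month score that leaves out the baseline value. Baseline non-response cannot then remove anyone from it.
6. Deal separately with people who also lack the 6-month score. Filling a covariate recovers none of them, so they need missing-outcome handling, which may already be in the full plan.

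The cost is revised wording and a small amount of extra analysis, with no new data. The reported missing-data rate will be higher, and the unadjusted check will be slightly less precise than the ANCOVA.

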### Data collection

All data of main- and short-assessments are self-reported data and will be collected and stored in the Research Electronic Data Capture (REDCap) software (83) at the University Hospital Basel. With the exception of the eligibility screening, participants will enter their own data online. Eligibility screening data is entered by the study nurse. Randomization of participants to either control or experimental group with a 1:1 allocation is also conducted in REDCap.

Cannabis sales data in pharmacies will be collected in a separate software named Cannavigia that traces the entire cannabis supply network (84). Participants are registered in Cannavigia and receive a unique identifier to ensure data collection to be as anonymous as possible. A separate list of identifiers linked to personal information is only accessible for study physicians and study nurses. Datasets of both softwares will be used for analyses.

### Data monitoring and auditing

A risk-based monitoring will be conducted to ensure the quality control. Based on the “Guidelines for risk-based monitoring,” the risk was estimated low (85). The study investigators conducted an initiation visit at the study center before eligibility screenings have started. Additionally, they will monitor the survey data in REDCap on a regular basis. Furthermore, a monitor, who is independent of the study organizers, will conduct three visits in four randomly selected pharmacies in order to ensure comparable study procedure in the pharmacies. The first visit will be conducted after cannabis access has started, the second one after 6 months, and the third after the final cannabis product was sold.

### Safety

We do not expect increased health risks for participants, since participants must already be regular cannabis users prior to study participation. In case of serious adverse events (SAE), the research team will be notified. Additionally, participants will be asked in every online-assessment whether they have experienced a SAE since the last assessment (life-threatening event, hospitalization longer than 24 h). The relation of any SAE to study procedures will be investigated and reported to the local ethics committee.

## Discussion

Various states have legalized cannabis for recreational use and further countries propose to legalize cannabis in the near future. Implemented regulatory approaches vary widely ranging from commercial market to strict regulation by the government (11). Existing evidence on the public health impact of recreational cannabis regulation is contradictory and inconclusive. Some studies have shown an association between the regulation of cannabis for recreational use and increased frequency of cannabis use among adults (15, 16), whereas others have shown no relation or a relation with increased three-month prevalence (21, 22). A recent systematic review has suggested that past-month cannabis use in adults (> 26 years) has increased after recreational cannabis legalization, whereas young adults (18–26 years) and adolescents (12–17 years) did not show an increase in past-month cannabis use (86). However, existing evidence is mainly based on observational data evaluating pre-post-legalization or comparisons between states with and without cannabis legalization. These study designs do not allow to derive causal relations. Furthermore, evidence on the impact of cannabis regulation on mental and physical health is largely lacking. Hence, there is still considerable uncertainty regarding the positive and negative health effects of cannabis regulation. Scientific evidence on policy options and their public health impact is needed.

In Switzerland, cannabis for recreational use is prohibited, but the Federal Act on Narcotics and Psychotropic Substances allows scientific studies with cannabis since 2021 (48). The aim of this law is to increase evidence-based knowledge of the advantages and disadvantages of different regulatory approaches, and thus, to provide a scientific basis for discussions about future cannabis policy in Switzerland. To our knowledge, the present study “Weed Care” is the first randomized controlled trial that evaluates the effects of recreational cannabis regulation compared to the illicit market on problematic cannabis use as well as on mental and physical health outcomes. This study design will provide compelling evidence elucidating benefits and harms of recreational cannabis regulation on relevant health indicators. For example, if results show that cannabis use and health outcomes improve after 6 months in the group with legal access compared to the control group, policymakers may consider the evaluated type of cannabis regulation to be superior to the prohibition. Besides improved users’ health, an additional benefit might be decreasing health costs in the long-term. However, this is not part of the present study. If results show no difference in health outcomes between the two groups, the analyzed regulation model is not inferior to prohibition and may still display a potential alternative approach for drug policy since prohibition has not achieved its aims over the last decades. In contrast, if results show that cannabis use and health outcomes deteriorate in the group with legal cannabis access compared to the control group, policymakers may draw the conclusion that these results favors cannabis prohibition. However, all conclusions should be drawn with caution, since the present study investigates one potential regulation model and its effect on health outcomes. Further research is needed to investigate the effects of regulated cannabis on additional outcomes such as on youth, criminality, stigmatization, or illicit market. Moreover, the evaluation of other regulation models such as cannabis social clubs or cannabis shops is substantial in order to compare the benefits and harms of different regulation approaches.

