To our knowledge, there is no randomized controlled study evaluating the effects of recreational cannabis legalization compared to the illicit market on relevant health outcomes. Available evidence is based on observational studies, including pre-post-legalization comparisons or comparisons between states with recreational cannabis regulation and states without. However, these study designs are not able to distinguish between secular trends and changes due to cannabis regulation and thus, causality remains unclear (47). The aim of the present randomized controlled study is to investigate the effects of cannabis regulation for recreational purposes compared to the illicit market on problematic cannabis use, mental disorders, and physical health. Although cannabis for recreational use is prohibited in Switzerland, scientific studies on recreational cannabis are allowed since 2021 (48). Hence, Switzerland offers a unique opportunity to gain scientific knowledge about alternative cannabis regulation approaches. We hypothesize that regulated cannabis access in pharmacies will reduce problematic cannabis use as within a regulated approach several conditions are available to facilitate lower-risk use and treatment. Furthermore, we hypothesize that regulated cannabis access will improve mental and physical health outcomes.

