### Sample size

The sample size was calculated on the basis of the primary hypothesis. A reliable change in problematic cannabis use is defined as a change of two points or greater in mean CUDIT-R after 6 months (65). The power analysis (power of 0.8, alpha of 0.05, dropout of 20%) identified a target enrollment of 374 cannabis users—187 per group—to detect a reliable change in problematic cannabis use after 6 months.

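### The Discussion reads a finding of no difference as showing that the regulation model is not inferior, a conclusion that a superiority trial with no margin cannot support

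*Protocol article*

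**What the plan says.** The Design section describes the study as "designed as a randomized, controlled, unblinded superiority trial with two parallel groups". The hypothesis at the end of the Introduction points one way: "We hypothesize that regulated cannabis access in pharmacies will reduce problematic cannabis use". The same paragraph adds a hypothesis of better mental and physical health.

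The Sample size section takes as its target "a change of two points or greater in mean CUDIT-R after 6 months", with "power of 0.8, alpha of 0.05, dropout of 20" per cent, and reports that this "identified a target enrollment of 374 cannabis users—187 per group—to detect a reliable change in problematic cannabis use after 6 months". Under Statistical methods, "For the analysis of the primary outcome, analysis of covariance will be used", with baseline CUDIT-R as covariate. The article contains no non-inferiority or equivalence hypothesis and no margin.

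The Discussion then sets out three possible results and the policy reading of each. For the middle one it says: "If results show no difference in health outcomes between the two groups, the analyzed regulation model is not inferior to prohibition". It goes on to say that the model might still be an alternative for drug policy. Later in the paragraph it asks for caution, on the ground that only one regulation model is being studied.

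**The concern.** A superiority test asks whether the data are inconsistent with equality. If they are not, equality is one possibility among several, and a real worsening is another. To say that a model is not inferior, one must rule out a worsening of a stated size, and no size is stated.

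The reading matters because the trial is meant to inform policy and a null is one of the three results the authors foresee. If the sentence were carried into the results paper, an imprecise null could be taken as evidence that legal access does no harm.

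The sentence also covers health outcomes in general. The sample size concerns CUDIT-R only, so for depression, anxiety, psychosis risk or respiratory symptoms the article gives neither a margin nor any indication of what differences the trial could detect.

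**Working it through.** **Inputs.** From Sample size: target difference 2 points, power 0.80, alpha 0.05, dropout 20%, 187 per group. From Data collection: "Randomization of participants to either control or experimental group with a 1:1 allocation". Not given: the SD, the sidedness of the test, and the correlation r between baseline and 6-month CUDIT-R. I assume a two-sided test, which fits the Discussion's own scenario of deterioration.

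**Step 1: what needs no SD.** Power of 80% for 2 points means a 20% chance of a non-significant result at a true 2-point difference. A two-sided test is symmetric, so the same holds for a true worsening of 2 points: about one trial in five.

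**Step 2: the plan's figure.** With no SD stated, 374 cannot be reproduced independently, only solved backwards. Completers per arm: 187 × 0.8 = 149.6, so 149 whole participants; in the other direction 149 / 0.8 = 186.25, rounded up to 187. Then

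SD = 2 / [(1.960 + 0.842) × √(2/149)] = 6.16.

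So 374 is internally consistent with an SD of about 6.16. A one-sided alpha would imply about 6.94.

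**Step 3: precision.** Unadjusted SE = 6.16 × √(2/149) = 0.714. The 95% half-width is 1.96 × 0.714 = 1.40. A result on the edge of significance in the harmful direction has an estimate of +1.40 and an upper limit of 2 × 1.40 = +2.80. ANCOVA multiplies the SE by √(1 − r²). The chance of a non-significant result at a true worsening d is close to Φ(1.96 − d/SE).

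| r (assumed) | SE | Half-width | Largest upper limit under a null | Non-significant at true +1 | Non-significant at true +2 |
|---|---|---|---|---|---|
| 0 | 0.714 | 1.40 | +2.80 | 71% | 20% |
| 0.5 | 0.618 | 1.21 | +2.42 | 63% | 10% |
| 0.6 | 0.571 | 1.12 | +2.24 | 58% | 6% |
| 0.7 | 0.510 | 1.00 | +2.00 | 50% | 2.5% |
| 0.8 | 0.428 | 0.84 | +1.68 | 35% | 0.3% |

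The rows with r above 0 apply if 374 was calculated without baseline adjustment. If adjustment was already built in, 6.16 is the residual SD and the first row describes the planned ANCOVA.

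**Step 4: sensitivity to SD.** With 149 per arm and no adjustment, an SD of 4 gives a half-width of 0.91 and a largest upper limit of about +1.8; an SD of 8 gives 1.82 and about +3.6.

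**The case against.** The strongest reply is that this is commentary. The sentence is one of three illustrative scenarios in a Discussion, its policy consequence is hedged, and the analysis section contains no such rule. It says no difference, not no significant difference. A superiority trial needs no non-inferiority margin, and rules for reporting intervals usually sit in a SAP, which is not shown.

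Much of that stands. A reader might infer that the plan fixes how a null will be reported, namely as evidence of no harm. The documents do not say so; that is an inference from the Discussion. The missing margin is not a defect in itself either. What remains is the flat statement that the model is not inferior. It is worded more firmly than the readings of the other two results, which only say what policymakers may conclude. The caution in the paragraph does not concern power, precision or null results. And since an observed difference is hardly ever exactly zero, no difference will in practice mean a non-significant one.

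Three further readings go too far:

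- *A null always leaves a 2-point worsening open.* It does not. Under the back-solved SD, at r of about 0.70 or more, a non-significant ANCOVA excludes +2. At r = 0 the estimate must exceed about 2 − 1.40 = +0.6 before +2 lies inside the interval.
- *Differential dropout pushes the result towards no difference.* Its direction is unknown. The Limitations section says only that control-group dropout may be high.
- *The 2-point target can serve as the harm margin, with 80% power.* The documents never call 2 points a tolerable worsening, and the 80% is circular because the SD was solved from 80% power at 2 points.

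**Conclusion.** The concern holds as a fault in a pre-stated interpretation. The inference from no difference to not inferior is invalid whatever the SD, because nothing in the article defines the worsening to be excluded.

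Its size for CUDIT-R is conditional. The one-in-five figure rests on the stated power and a two-sided test. The 71% and 58% figures also need the back-solved SD, and the 58% an assumed correlation. The amount of harm still open after a null cannot be fixed from the article, because it moves with both unknowns. For the secondary outcomes it cannot be quantified at all.

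Severity is should-fix. The hypothesis, sample size, endpoint and primary analysis are unaffected, and nothing here shows that the trial is too small for its stated purpose.

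**What to change.** Remove the clause saying the model is not inferior to prohibition, and put in its place, in the results paper and in the SAP if it covers interpretation:

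*A non-significant difference is inconclusive. It will be interpreted from the 95% confidence interval of the adjusted difference between groups, for each outcome.*

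If the sponsor wants to be able to claim absence of relevant harm, it should justify a margin for each outcome concerned and fix it before the 6-month results are seen. A margin chosen afterwards would not be credible. The 2-point superiority target should not become that margin by default.

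The cost is a sentence, with no change to enrolment, data collection or the primary analysis. The downside is that some null results will have to be reported as inconclusive, which is a less convenient message for policy.
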